### Secondary Outcomes

The secondary outcomes are the changes between baseline (T0) and follow-up after 6 months (T1) in:

Structural MRI (eg, gray and white matter volume, ventricular enlargement, abdominal adipose tissue T1 assessment), neurochemical assessment of neuroinflammation in dlPFC and hippocampus (using MRS) and whole brain analyses of primary neuroimaging outcomes (BOLD activity during working memory, cerebral perfusion);Anthropometric measurements (eg, BMI, waist-to-hip ratio) and blood pressure;Cognitive test performance scores of cognitive domains predominantly affected by cognitive aging (executive functioning, working memory, and processing speed) as measured by a neuropsychological test battery (NTB) containing: (1) Rey Auditory Verbal Learning Test (RAVLT) [126], (2) Verbal Fluency Test (VFT) [127], (3) Trail Making Test (TMT) part A&B [128], (4) Digit Symbol Substitution Test (DSST) [129], and (5) Digit Span Test (DST) [129];Lifestyle domain-related questionnaire scores for (1) diet (MIND-adjusted Eetscore [130]), (2) physical activity (Short Questionnaire to Assess Health-enhancing Physical Activity (SQUASH) [131], LASA Sedentary Behavior Questionnaire (SBQ) [132] and SARC-F Sarcopenia Questionnaire [133]), (3) stress management & mindfulness (Perceived Stress Scale (PSS) [134], Hospital Anxiety and Depression Scale (HADS) [135], Five Facet Mindfulness Questionnaire (FFMQ) [136]), (4) cognitive training (Cognitive Failures Questionnaire (CFQ) [137] and Metamemory In Adulthood Questionnaire (MIA) [138]), (5) sleep (Pittsburgh Sleep Quality Index (PSQI) [139]).Physiological parameters measured on the wrist using a smartwatch over a 7-day period (day and night), including galvanic skin response, skin temperature, and heart rate parameters (measured by photoplethysmography sensing), and contextual motion parameters (measured by an integrated 3-axis accelerometer and 3-axis gyroscope);Fecal analysis, including intestinal transit time [140], stool water content, pH, microbiota composition (both relative- and absolute abundances), metabolite profiles, and inflammatory biomarkers;Blood analysis, including intestinal integrity markers, inflammatory markers, cardio-metabolic and oxidative stress markers, nutritional status, (early) AD markers, and dietary- and microbiota-derived metabolites;Breath analysis to measure SIBO [141,142].

### Other Study Parameters

Other study outcomes include the following:

Baseline demographics (age, sex, education level, ethnicity, etc) and medication history;Baseline intracranial myelin and iron deposition measured by quantitative susceptibility mapping (QSM) MRI, and by relaxation rates (R_1_ and R_2_*– longitudinal and apparent transverse relaxation rates respectively);Baseline IQ based on the Dutch Adult Reading Test (DART) [143];Intervention adherence (in the high-intensity group) during the intervention period: group meeting attendance and completion of provided exercises;Changes between baseline (T0) and follow-up after 6 months (T1) of the Montreal Cognitive Assessment (MoCA) [144];Urine analysis of microbiota-derived bioactive compounds (changes between baseline (T0) and follow-up after 6 months (T1);Changes between baseline (T0) and follow-up after 6 months (T1) in other health or lifestyle-related questionnaire scores, including (1) (psychosocial) complaints in daily life (Dutch Four Dimensional Complaint Questionnaire [145]), (2) quality of life (EQ-5D-5L [146]), (3) modifiable dementia risk score (“Lifestyle for BRAin health (LIBRA) [147]), (4) social contact and perceived social support (Lubben Social Network Scale [148]), (5) cognitive coping strategies (Cognitive Emotions Regulation Questionnaire [149]), (6) apathetic symptoms (Starkstein Apathy Scale [150]), (7) gastrointestinal symptoms rating scale (GSRS) [151], and (8) stool consistency (Bristol Stool Scale [152]).

### Sample Size

The expected effect size for this study was determined based on other, mostly single-domain, lifestyle intervention studies with similar outcomes as our primary outcomes in the brain (eg, cerebral perfusion, working memory assessments) and in the periphery (eg, immunometabolic biomarkers, gut microbiome diversity). These studies generally found medium-to-large effect sizes (see Table S4 in Multimedia Appendix 1 [52,53,95,106,107,153-161]). Therefore, we deemed a slightly above-medium effect size of 0.30 (Cohen f[V]) suitable for our primary outcomes from baseline (T0=week 0, before start intervention) to follow-up (T1=week 26, after end intervention). The sample size calculation was performed using G*Power (version 3.1.9.6; Universität Kiel [162]). Using a multivariate ANOVA (with repeated measures and within-between interaction) *F* test with a power of 80% and a 2-tailed α-error probability of .05, we calculated that a total of 90 study participants would be required. However, based on our experience with previous fMRI and intervention studies, we expect a potential loss of data of 15% due to poor fMRI data quality (eg, motion artifacts) and potential intervention drop-outs. Therefore, to reach sufficient power, we would require a total sample size of 104 (90 participants×15% potential data loss=103.5=104) participants in this study.

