## Methods

### Trial Design

The HELI study is a multicenter randomized controlled trial, aiming to investigate the effects of a 6-month multidomain lifestyle intervention on brain functioning and its relation with immunometabolic markers in aging. Powered to include 104 total participants, HELI has two parallel-arm treatment groups: (1) a supervised “high-intensity” coaching intervention group with weekly group meetings, lifestyle-related information and exercises, and (2) a nonsupervised “low-intensity” coaching intervention group, receiving information leaflets every 2 weeks. Because the participants of the high-intensity intervention arm were supervised in a group context, we recruited and subsequently randomized participants in 4 different inclusion waves (between May 2022 and October 2023), consisting of 19‐32 participants. Participants partook in outcome measure visits at baseline (T0) and at 6 months follow-up (T1) (see Figure 2).

The HELI study has been reviewed and accepted according to the Medical Research Involving Human Subjects Act (“Wet Medisch-wetenschappelijk Onderzoek met mensen” in Dutch) by an accredited Medical Research Ethics Committee (MREC), the MREC Oost-Nederland on December 2, 2021 (ToetsingOnline filenumber NL78263.091.21, ClinicalTrials.gov ID NCT05777863).

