### Methods: Randomization and Blinding

Participants were randomized per inclusion wave, using stratified (2,4) block-randomization to provide a 1:1 allocation between our two intervention arms. Randomization was stratified by the factors sex (male vs female), risk factor profile (medium risk 2‐3 points vs high risk ≥4 points), and a combined factor of education level +age (70+ yearsor low education vs 60‐69 years and high education, specified as university of applied science associate degree (Dutch: HBO associate degree or higher). As with our sample size, (2,4) block-randomization was only possible with up to 3 strata, age, and education were combined in one stratification factor as they are both important covariates of cognitive functioning and aging-related cognitive decline [163].

An independent researcher from the DCCN was authorized to manually perform the randomization. This authorized researcher had no affiliation with the project and therefore had no bias in the allocation procedure.

Given the nature of the intervention arms, the participants and intervention supervisor were unable to remain blinded to the assignment to the intervention arms. Researchers conducting the follow-up outcome measure visits remained blinded and unaware of the intervention arm allocation. Only in case of unforeseen circumstances would deviations be made (eg, an unblinded researcher conducting the MRI protocol). Neuropsychological tests and task trainings (ie, n-back task) were conducted by a blinded researcher in all cases. Participants were asked to refrain from speaking about the intervention contents and experience during the follow-up outcome measure visits to prevent accidental unblinding.

The requirement for emergency unblinding was not applicable to this study, as participants were unblinded to the group allocation and the nature of the study setting.

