## Results

This work was supported by a Crossover grant (MOCIA 17611) of the Dutch Research Council (NWO), granted in December 2019. Recruitment started in April 2022 and concluded in October 2023. Over this period, a total of 279 people showed interest in participating and enrolled, of which 269 participated in the first round of telephone screening and 235 participated in the second round of telephone screening (see Figure 4). We were able to initially include our goal sample size of 104 participants, but 2 last-minute cancellations resulted in a final included sample size of 102 older Dutch adults. This sample size was subsequently randomized in the two parallel intervention arms, with n=49 participants in the “low-intensity” intervention group and 53 participants in the “high-intensity” intervention group.

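### The 15% data-loss allowance multiplies 90 by 1.15 instead of dividing by 0.85, so neither the planned 104 nor the 102 randomised leaves the required 90 analysable

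*Protocol article*

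**What the plan says.** The Sample Size section of the protocol article bases the calculation on a "multivariate ANOVA (with repeated measures and within-between interaction" in G*Power, with an effect size f(V) of 0.30, 80% power and "a 2-tailed α-error probability of .05". It arrives at 90 participants. It then expects 15% of the data to be lost to poor fMRI quality and drop-out from the intervention, and concludes: "we would require a total sample size of 104 (90 participants×15% potential data loss=103.5=104) participants in this study".

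The result is carried forward as a design claim. Trial Design says "Powered to include 104 total participants", and the Abstract and Recruitment sections use the same number. The Results section reports that 104 were first included but that "2 last-minute cancellations resulted in a final included sample size of 102 older Dutch adults", split 49 and 53 between the arms. Methods: Statistics and Analysis adds that missing or poor-quality data will be left out of the analysis.

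**The concern.** The 15% is described as a share of the data that will be lost, so it applies to the number enrolled. The calculation instead adds 15% of the number needed at the end. These differ: adding 15% to 90 and then losing 15% of the total does not return to 90. The expression as printed does not hold either, since 90 × 15% is 13.5, although 103.5 makes the intended 90 × 1.15 clear.

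At stake is whether the trial has the stated 80% power under its own assumptions, and how much data loss it can absorb. A reader would take it that a 15% loss is covered. That matters when a null primary result is interpreted.

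**Working it through.** **Inputs**

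- Two-sided alpha 0.05, power 80%, f(V) = 0.30, repeated-measures MANOVA, within-between interaction (Sample Size).
- Two arms, "to provide a 1:1 allocation between our two intervention arms" (Methods: Randomization and Blinding).
- Two measurements, T0 and T1 (Trial Design).
- Required analysable number 90, expected loss 15%, inflated number 104 (Sample Size).
- Number randomised: 102 (Results).

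The article does not print the number of groups and measurements entered in G*Power. I assumed 2 and 2, which match the design.

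**Step 1: reproduce the 90.** With two groups and two time points the interaction test is F with 1 and N − 2 degrees of freedom. The noncentrality is λ = N × f(V)² = N × 0.30² = 0.09N. Power is the probability that this noncentral F exceeds the central 5% critical value.

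| N analysable | Power |
|---|---|
| 90 | 80.4% |
| 89 | 79.9% |
| 88 | 79.5% |
| 87 | 79.0% |
| 86 | 78.5% |

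The smallest N with at least 80% power is 90, so the plan's base figure reproduces exactly and carries no spare margin.

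**Step 2: reproduce the 104.** 90 × (1 + 0.15) = 103.5, rounded up to 104. This is the only route that gives the printed 103.5.

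**Step 3: the inflation that keeps 90.** If a fraction d of those enrolled is lost, the number to enrol is n/(1 − d):

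- 90/(1 − 0.15) = 90/0.85 = 105.88, rounded up to 106.
- Check: 106 × 0.85 = 90.1.

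**Step 4: what remains at 15% loss.**

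- 104 × 0.85 = 88.4, so about 88 analysable and 79.5% power.
- 102 × 0.85 = 86.7, so 86 to 87 analysable and 78.5% to 79.0% power.

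**Step 5: the loss each number tolerates.**

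- With 104: 1 − 90/104 = 13.5%.
- With 102: 1 − 90/102 = 11.8%.

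**Step 6: effect of the 49/53 split.** The efficiency relative to equal arms is 4 × 49 × 53/102² = 10388/10404 = 0.998, so the imbalance does not change the picture.

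**The case against.** The arithmetic is hard to dispute, so the case on the other side is about weight.

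- **The effect is tiny.** The planned target is short by two participants, and power drops by less than one percentage point. The effect size of 0.30 is itself a rounded judgement and a larger source of uncertainty. This stands, and limits the point to a minor correction.
- **The 102 has a separate cause.** Two late cancellations, openly reported, took the number from 104 to 102. The formula accounts for two of the four participants by which 102 falls short of 106, and the cancellations for the other two. This also stands. The 102 still belongs in a corrected power statement, because it is the number the trial has.
- **Actual loss may be below 15%, at least for some outcomes.** People who stop the intervention without withdrawing consent are invited to T1 and their data are used. A poor scan does not remove the blood or fecal primary outcomes. For those, loss under 11.8% is plausible and 90 could be reached. The shortfall is therefore clearest for the fMRI outcomes. But 15% is the plan's own allowance, applied to the whole sample, and 104 was meant to cover it.
- **The mixed model can use participants with one usable time point.** The power figures above treat every lost participant as contributing nothing, so they are slightly pessimistic. The plan nevertheless set its target as 90 after loss, and by that standard it falls short.

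None of this supplies a reason for the factor 1.15, and the article states no other margin.

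**Conclusion.** The concern holds. The base figure of 90 is right; the allowance for loss is not. The correct number is 106, against 104 planned and 102 randomised. At 15% loss, power is about 1 percentage point lower than with 90 analysable if 104 are enrolled, and 1.4 to 1.9 points lower with 102 (80.4% less 79.0% or 78.5%). In both cases it is below the stated 80%.

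These figures are for a single primary outcome at f(V) = 0.30 and two-sided alpha 0.05. They assume that 15% of participants are lost in full for that outcome. If loss is at most 11.8%, the 102 randomised still give 80% power. The error does not threaten the validity of the trial, but the sample size and the loss it is said to cover are wrong as printed and should be corrected.

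**What to change.** Replace the inflation step in Sample Size with 90/(1 − 0.15) = 105.9, rounded up to 106. Add that with 102 randomised and 15% loss, 86 to 87 participants are expected to be analysable, giving 78.5% to 79.0% power for one primary outcome at f(V) = 0.30, and that 80% power holds only if loss is no more than 11.8%. Adjust the claims of being powered at 104 in the Abstract and Trial Design to match. When results are reported, the analysable number for each primary outcome should be set against 90.

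The cost is a corrected sentence or two and a slightly less favourable power statement. Recruitment is complete, and no further enrolment or change of design is proposed.

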### Methods: Randomization and Blinding

Participants were randomized per inclusion wave, using stratified (2,4) block-randomization to provide a 1:1 allocation between our two intervention arms. Randomization was stratified by the factors sex (male vs female), risk factor profile (medium risk 2‐3 points vs high risk ≥4 points), and a combined factor of education level +age (70+ yearsor low education vs 60‐69 years and high education, specified as university of applied science associate degree (Dutch: HBO associate degree or higher). As with our sample size, (2,4) block-randomization was only possible with up to 3 strata, age, and education were combined in one stratification factor as they are both important covariates of cognitive functioning and aging-related cognitive decline [163].

An independent researcher from the DCCN was authorized to manually perform the randomization. This authorized researcher had no affiliation with the project and therefore had no bias in the allocation procedure.

Given the nature of the intervention arms, the participants and intervention supervisor were unable to remain blinded to the assignment to the intervention arms. Researchers conducting the follow-up outcome measure visits remained blinded and unaware of the intervention arm allocation. Only in case of unforeseen circumstances would deviations be made (eg, an unblinded researcher conducting the MRI protocol). Neuropsychological tests and task trainings (ie, n-back task) were conducted by a blinded researcher in all cases. Participants were asked to refrain from speaking about the intervention contents and experience during the follow-up outcome measure visits to prevent accidental unblinding.

The requirement for emergency unblinding was not applicable to this study, as participants were unblinded to the group allocation and the nature of the study setting.

### Methods: Statistics and Analysis

We will test for change between T0 and T1 in the primary and secondary outcome variables, both within-group and between-group, using linear mixed-effect models with random effects for intercept (individuals). The intervention group and time will be included as fixed effects, as well as the interaction term between intervention group and time, to model the difference in change between T0 and T1 as a function of group allocation.

In addition, we will test for correlations in change (T0 minus T1) between (primary) brain outcomes and (primary) peripheral outcomes. We will select an appropriate correlation test for our data, based on whether assumptions are met. We will include both the high- and low-intensity groups if there is enough variance in change across both groups; else, we will only include the high-intensity group.

The level of significance will be set at 0.05 (2-sided). FDR correction will be used to account for multiple comparisons of secondary and exploratory outcomes. FWE correction will be used for secondary whole-brain analyses.

As part of exploratory analyses to assess the domain-specific effects on our primary outcome measures, we will take the pre- and posteffects of the primary outcome measures and use domain-related questionnaire scores and smartwatch-derived physiological data as a measure of improvement for each respective domain as predictors in linear mixed-effect models.

We will perform an intention-to-treat analysis. Participants who withdrew from the study during the 6-month intervention period, but had not withdrawn consent, were invited to the T1 (after week 26) follow-up outcome assessments. This means that we will use all available collected data, including collected (follow-up) data of participants who dropped out of the intervention. Missing data or data with insufficient quality, however, will not be used in the analysis.

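### The primary model leaves out the factors used to stratify randomisation; if they predict change, the group×time test is mildly conservative and loses a little power.

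*Protocol article*

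**What the plan says.** Under Methods: Randomization and Blinding: "Participants were randomized per inclusion wave, using stratified (2,4) block-randomization". The same section continues: "Randomization was stratified by the factors sex (male vs female), risk factor profile" (2-3 against 4 or more points), with age and education merged into a third factor. The reason given for using age and education is that "they are both important covariates of cognitive functioning and aging-related cognitive decline". Trial Design puts the number of waves at four, with 19 to 32 people in each.

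Under Methods: Statistics and Analysis, change in the primary and secondary outcomes is to be tested "using linear mixed-effect models with random effects for intercept (individuals"). The fixed effects named are intervention group, time and their interaction. The interaction carries the treatment comparison. Neither wave nor any stratification factor appears. The Discussion remarks that education is a frequent covariate for task-related neuroimaging and neuropsychological data, but treats this as a matter of interpretation and adds no term to the model.

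**The concern.** Stratified allocation makes the arms more alike on the stratifying factors than simple randomisation would. If those factors are related to the quantity being compared, the true sampling variability of the treatment estimate falls. A model without them still counts their contribution as residual noise, so its standard error is too large: the test rejects less often than its nominal level and some power is wasted.

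The quantity compared here is the difference in change between arms, so what matters is whether the factors predict change. Power is not generous: the trial is sized for 80% with 90 evaluable people, and 102 were randomised.

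**Working it through.** **1. The plan's own figure.** Inputs from Sample Size: "we deemed a slightly above-medium effect size of 0.30 (Cohen f[V]) suitable for our primary outcomes"; an *F* "test with a power of 80% and a 2-tailed α-error probability of .05"; and "a total of 90 study participants would be required". For the within-between interaction with two groups and two visits, the test is a noncentral F with df1 = 1, df2 = N − 2 and λ = f(V)² × N. At N = 90, λ = 0.09 × 90 = 8.1 and power is 0.804; at N = 89 it is 0.799. The stated 90 is reproduced. With equal arms, λ = (δ/2)² × N, so f(V) = 0.30 corresponds to δ = 0.6 standard deviations of change.

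**2. What the planned model tests.** With two visits, complete data and a random intercept, the group×time term is the difference in mean T1 − T0 change. Stable level differences by sex, risk, age/education or wave cancel. Mixed models fitted to one simulated data set of 102 people, in which sex and age/education were made to predict change, gave:

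| Fixed part | group×time | SE |
|---|---|---|
| group×time only | 0.10914 | 0.20935 |
| plus factors as main effects | 0.10914 | 0.20935 |
| plus factor×time terms | 0.16008 | 0.18756 |

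With 15% of T1 values missing, main effects moved the SE only from 0.2285 to 0.2273; factor×time terms brought it to 0.1996.

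**3. Price of adjusting when nothing is gained.** Sex, risk and age/education take 3 degrees of freedom and four waves take 3, so 6 in all. At N = 90 with R² = 0, df2 falls from 88 to 82 and power from 0.804 to 0.803. At 102 × 0.85 ≈ 87 evaluable, it falls from 0.790 to 0.789.

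**4. The stratified design itself.** There are 2 × 2 × 2 × 4 = 32 cells for 102 people, or 102/32 ≈ 3.2 each, so many blocks of 2 or 4 stay incomplete and balance is only partial. The design was therefore simulated directly: permuted blocks of 2 and 4 within stratum and wave, N = 102, 4000 replicates per scenario, change analysed with and without the six terms. The 65.7% female share comes from the article. Assumed are 22% high risk, 55% in the older/lower-education stratum, four waves of about 25, and additive factor effects of equal size. R² is the share of variance in change explained by the factors, also assumed. Power is for δ = 0.6.

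| R² of change | Type I error, planned | Type I error, adjusted | Mean model SE vs true SD, planned | Power, planned | Power, adjusted |
|---|---|---|---|---|---|
| 0 | 5.4% | 5.7% | 0.198 vs 0.201 | 0.848 | 0.843 |
| 0.05 | 5.1% | 5.3% | 0.198 vs 0.197 | 0.848 | 0.859 |
| 0.10 | 4.1% | 5.4% | 0.198 vs 0.192 | 0.863 | 0.884 |
| 0.20 | 3.1% | 4.7% | 0.198 vs 0.182 | 0.877 | 0.918 |

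Simulation error at a 5% rate is √(0.05 × 0.95/4000) ≈ 0.34 percentage points, so the adjusted rates lie within about two such errors of 5%. Adjustment gains 0.884 − 0.863 = 2.1 points at R² = 0.10 and 0.918 − 0.877 = 4.1 points at 0.20. It costs 0.848 − 0.843 = 0.5 points at R² = 0.

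The power formula with λ/(1 − R²) and df2 = N − 8 gives larger adjusted values at N = 90 (0.843 and 0.882, against 0.804 unadjusted). That comparison treats the unadjusted analysis as if allocation had been simple. Stratification already delivers part of the gain, so the simulated differences are the ones to use.

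**The case against.** Three objections carry weight.

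- **The harm is conditional.** The article links age and education to cognitive function and decline. It does not say that these, sex, risk score or wave predict six-month change in fMRI activation, blood flow, inflammation markers or microbiota diversity. At R² = 0 nothing is lost. This stands, and the point is worded accordingly.
- **Any error is on the safe side.** Type I error falls below 5%, never above it because of this omission. This also stands.
- **A separate analysis plan may add covariates.** It may. But the article does not defer the model terms; it writes out the fixed and random parts, and that model omits the design factors.

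A reader might infer more than the documents support:

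- That incomplete blocks and the 53:49 split leave imbalance and wave or season effects uncorrected. Randomisation was within wave, stable level differences cancel in change, and remaining chance imbalance is sampling error, not bias. The simulated design gave an average arm-size difference of about 3.7, so a difference of 4 is ordinary. Table 2 is not split by arm and shows no imbalance on any factor.
- That the share of outcome variance explained by the factors translates directly into a smaller standard error. In the planned model the random intercept already removes the stable part of that variance; only variance in change counts (or in T1 given baseline, for a baseline-adjusted model).

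**Conclusion.** The mismatch between design and model is real, and its effect is modest and conditional. If sex, risk stratum, age/education stratum and wave together explain 10-20% of the variance in change, the planned group×time test runs at about 4% to 3% instead of 5% and gives up about 2 to 4 points of power. At 5% the gain from adjusting is about 1 point; at zero, adjusting costs under 1 point. These figures rest on the assumed R², the assumed stratum shares and additive effects. The documents support neither a certain loss of precision nor an invalid or biased analysis. The case for changing the model is that protection costs almost nothing, while leaving the factors out can only waste information that the randomisation was built around.

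**What to change.** State in the statistics section that the primary model includes sex, risk stratum (2-3 against 4 or more), the age/education stratum and wave, each as a factor×time term alongside group, time and group×time. If a baseline-adjusted model of T1 is preferred, which is a separate choice from the one now written, the same factors go in as ordinary covariates. Adding them to the planned mixed model as main effects only is not enough, since that leaves group×time unchanged with complete data. One term per factor suffices; the 32 cells need not be modelled. The cost is a change of wording and about 6 degrees of freedom. No data collection changes.

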##### Group Sessions

The weekly group sessions were offered throughout the 6-month (26 weeks) intervention period. For 20 out of 26 weekly sessions, a specific lifestyle domain acted as the central theme for a given week (Figure 3). At week 1, after the baseline measurements of all participants in a wave and subsequent randomization had been concluded (T0), the intervention started off with an on-site introductory session.

The weekly group sessions provided participants with detailed lifestyle-related information, guidelines, exercises, and advice, as well as the opportunity for discussion with other group members and with the intervention supervisor. Weekly group sessions were guided by the intervention supervisor and were composed of the following recurring elements: social interaction, introductory question round, reiteration of previous lifestyle domains, dissemination, exercises, and a final question round (see Table S1 in Multimedia Appendix 1 for further details).

Over the 6-month intervention period, each of the five lifestyle domains was addressed in separate weekly group sessions (see Figure 3). We provided three distinct types of weekly group sessions:

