### Outcomes

All outcome measures were measured at baseline (T0) and after participation in the 6-month multidomain lifestyle intervention (T1), during visits at both research centers. Blood drawing and breath tests were performed in a fasted state. Some outcome measures, such as lifestyle domain or adherence-related questionnaires, were also collected throughout the intervention period. For a detailed overview of all outcomes and the collection schedule, see S4 in Multimedia Appendix 1.

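### The primary mixed model estimates a separate T0 mean in each arm, so it is a valid change-score comparison that is less precise than a baseline-adjusted analysis

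*Protocol article*

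**What the plan says.** Under Methods: Statistics and Analysis, the protocol article says that change in the primary and secondary outcomes will be tested "using linear mixed-effect models with random effects for intercept (individuals". On the fixed part it says: "The intervention group and time will be included as fixed effects, as well as the interaction term between intervention group and time". The purpose of the interaction is "to model the difference in change between T0 and T1 as a function of group allocation", so the interaction is the treatment effect. No T0 covariate and no equal-baseline constraint is stated.

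Two design facts matter here. Under Outcomes: "All outcome measures were measured at baseline (T0) and after participation in the 6-month multidomain lifestyle intervention (T1". So there is one pre-intervention and one post-intervention value per person. Under Group Sessions, the intervention starts "after the baseline measurements of all participants in a wave and subsequent randomization had been concluded (T0", so T0 comes before allocation.

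The Sample Size section is built on the same group-by-time test, with f(V)=0.30, 80% power and 90 evaluable participants. The total is raised to 104 because "we expect a potential loss of data of 15% due to poor fMRI data quality" and drop-out are anticipated.

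**The concern.** A group main effect in this model is the difference between arms at T0. Because T0 precedes randomisation, its true value is zero, and any observed difference is chance. The model still estimates that difference from the data and subtracts it when forming the interaction. Information that the design supplies at no cost, namely that both arms start from the same population mean, goes unused.

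At stake is precision. The planned N just reaches 80% power under this test, and enrolment has closed at 102. The choice of analysis is therefore one of the few remaining ways to narrow the confidence intervals, and the T0 values it needs are already collected.

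**Working it through.** **Inputs from the article.** f(V)=0.30, power 80%, N=90 and 15% data loss (Sample Size); two-sided α of 0.05 (Sample Size; Methods: Statistics and Analysis); 49 and 53 randomised (Results). **Assumed.** The T0–T1 correlation ρ, shown from 0.3 to 0.9; equal variances at T0 and T1; the change-score effect held at f=0.30 while ρ varies.

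**1. Reproduce the plan's figure.** For two arms and two visits the interaction test is F(1, N−2) with noncentrality λ = N·f². At N=90, λ = 90 × 0.09 = 8.1 and power is 0.804. At N=89 it is 0.799. The smallest N reaching 80% is 90, as stated. With two equal arms, f=0.30 is a standardised difference of 0.6 on the change score.

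**2. What the stated model is.** With complete pairs and a non-negative intercept variance, group + time + group×time with a random intercept gives the change-score comparison. On simulated data with the 49/53 split:

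| ρ | Mixed model, estimate (SE) | Change score, estimate (SE) |
|---|---|---|
| 0.5 | 0.7759 (0.1833) | 0.7759 (0.1833) |
| 0.7 | 0.5940 (0.1383) | 0.5940 (0.1383) |

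**3. How a chance T0 difference enters.** If the arms differ by Δ₀ at T0, the expected T1 difference is τ + ρΔ₀. Subtracting Δ₀ gives τ − (1−ρ)Δ₀. So a fraction 1−ρ carries into the estimate: 50% at ρ=0.5, 30% at 0.7 and 10% at 0.9.

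**4. Variance ratio.** Per person, Var(T1−T0) = 2σ²(1−ρ). The residual variance of T1 given T0 is σ²(1−ρ²). The ratio is (1−ρ²)/[2(1−ρ)] = (1+ρ)/2. Over 4,000 simulated trials per value, the ratio was 0.68, 0.74, 0.86 and 0.95 at ρ=0.3, 0.5, 0.7 and 0.9, against 0.65, 0.75, 0.85 and 0.95 in theory.

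**5. Power after baseline adjustment.** Divide f² by the ratio and spend one more degree of freedom. At ρ=0.5, for example, λ = 8.1/0.75 = 10.8 on F(1, 87).

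| Assumed ρ | Variance ratio | CI narrower by | Power at N=90 (stated model 0.804) | N for 80% | Raw effect implied, 0.6·√(2(1−ρ)), in SD |
|---|---|---|---|---|---|
| 0.3 | 0.65 | 19% | 0.937 | 59 | 0.71 |
| 0.5 | 0.75 | 13% | 0.901 | 68 | 0.60 |
| 0.7 | 0.85 | 8% | 0.863 | 77 | 0.46 |
| 0.8 | 0.90 | 5% | 0.843 | 81 | 0.38 |
| 0.9 | 0.95 | 2.5% | 0.823 | 85 | 0.27 |

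At ρ=0.5 the stated model would need 90/0.75 = 120 people to match the precision of 90 with adjustment.

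**6. At the enrolled number.** 102 × 0.85 = 86.7. At N=86 the stated test has power 0.785; with adjustment it is 0.888, 0.847 and 0.805 at ρ=0.5, 0.7 and 0.9.

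**7. Missing visits.** With 15% of T1 values missing at random, the stated mixed model had 0.94 (ρ=0.5) and 0.98 (ρ=0.7) of the variance of a complete-pair change score, so it recovers a little. A common-baseline model had 0.75 and 0.88 of the stated model's variance. Most of the possible gain is still unclaimed.

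**The case against.** The strongest reply is that nothing here is wrong. The outcomes are defined as changes, the power calculation uses the group-by-time test, and the analysis fits that same test. The three agree, N=90 reproduces, and the test is unbiased under randomisation at its nominal α. All of that stands. A reader might infer that the stated model is biased or mis-sized; the documents do not support that.

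Three other stronger readings also fail:

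- **That baseline imbalance passes into the estimate in full.** Only the fraction 1−ρ does (step 3), because stable differences between people cancel in the change.
- **That the stated model drops people with one usable visit.** A likelihood-based mixed model keeps them, and the article says all available collected data will be used. The constrained model has no advantage on this point.
- **That ANCOVA of T1 on T0 is interchangeable with the constrained model.** It is a close alternative for complete pairs. A complete-case ANCOVA loses anyone missing either visit, and it does not directly give the within-group change that the article also wants.

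The size of the gain is also open to challenge. No ρ is given, the figures rest on equal variances, and fixing f at 0.30 implies a raw effect that shrinks from 0.71 to 0.27 SD across the table. The gain is an average over trials: in the single simulated data set at ρ=0.7, the ANCOVA standard error was 0.1390 against 0.1383 for the change score. These points limit the claim but do not remove it.

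Finally, an unseen analysis plan may add baseline adjustment. That is possible, but the group main effect is stated explicitly in the article, so the point concerns a stated choice and not an omitted detail.

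**Conclusion.** The point holds as lost efficiency. The stated model is valid and consistent with its sample size, but it spends information on a T0 difference that randomisation makes zero in expectation. With equal variances, a baseline-adjusted analysis has (1+ρ)/2 of its variance. At N=90 and f=0.30 that is worth between about 13 percentage points of power at ρ=0.3 and 2 points at ρ=0.9. Which primary outcomes lie where in that range cannot be told from the article. The algebra is certain; the practical gain depends on ρ. The change is advisable and not a condition for the analysis to be sound.

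**What to change.** For each primary outcome, replace the stated fixed effects with a constrained longitudinal model: one common T0 mean (no group main effect), time and group×time, with an unstructured 2×2 within-person covariance so that unequal variances at T0 and T1 are allowed. The time coefficient is the change in the low-intensity arm, time plus interaction is the change in the high-intensity arm, and the interaction is the between-arm difference. All available visits are used. ANCOVA of T1 on T0 plus arm may be named as a close alternative for complete pairs only.

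No new data are needed and the planned N stands. The cost is procedural. The model has been published, and the article does not say whether T1 data have been examined. The change should therefore be a dated, documented amendment made before any unblinded analysis, with the model as published reported as a sensitivity analysis.
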